**13. Statistical analysis**

Descriptive statistics were provided for binary and continuous variables using incidence frequency (%) and mean ± standard deviation and range. McNemar tests were used to compare binary variables, and two-sample *t*-tests were used to compare continuous variables. Sensitivity, specificity, diagnostic accuracy, positive predictive value (PPV), and negative predictive value (NPV) of each needle were calculated based on per protocol analysis. Two-sided *P*-values were calculated and significance was accepted at 5%. All statistical analyses were performed using PASW Windows, version 18.0.0 (SPSS Inc., Chicago, IL, USA).

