Similar to EUS-FNA the feasibility and diagnostic yield of EUS-FNB depends on the location, size, and characteristics of target lesions in addition to technical and procedural factors (needle diameter and handling technique, material processing and expertise, and training and interaction between endosonographers and cytopathologists). Furthermore, technical limitations such as mechanical friction of the needle-firing mechanism in larger-caliber needles in the torqued trans-duodenal position, when applied to pancreatic head or uncinated process lesions, may occur with EUS-FNB [10-13]. For this reason, a similarly designed but more flexible FNB device has been developed using a 25-gauge needle platform [14]. Approximately 60% to 70% of diagnosed ductal adenocarcinomas occur in the pancreatic head or uncinated process, underscoring the need for an effective trans-duodenal approach. Furthermore, blood and cellular debris contamination complicate cytopathological interpretation, a common occurrence with the widely used 22-gauge needle.[15] In addition, it is often difficult to penetrate a calcified solid mass with a 22-gauge needle.[15] We hypothesized that a 25-gauge needle would provide an appropriate specimen while more easily penetrating solid pancreatic masses.

However, it is unclear whether the theoretical benefit of 25-gauge needles for EUS-FNB actually results in a higher procurement rate of high-quality histologic core samples compared to 22-gauge needles. Furthermore, no study has evaluated histologic core procurement rates of 25-gauge needles. Therefore, the aim of this study was to compare the efficacy of the recently developed 25-gauge EUS-FNB device to 22-gauge EUS-FNB for obtaining histologic core tissues in order to assess solid pancreatic masses.

[figure not shown]

Figure 1. 25-gauge Ultrasound biopsy needle (EchoTip® ProCore™ High Definition Ultrasound Biopsy Needle, Cook Medical Inc, Bloomington, IN)

Figure 2.

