**4. Summary of study design**

**Study design:** Single center, prospective, randomized, double-blinded corss-over study

**Study participants:** Planned number: set at 66 pairs

**Study centers:** Severance Hospital, Yonsei University College of Medicine, Seoul, Korea

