**5. Sample size calculation**

To calculate the sample size, we referred to the recent studies[19,21] using the same needle calibers as ours (EUS-FNB with the 25-gauge and 22-gauge needles). In the first study[19] conducted by Bang et al, proportion (%) of optimal histologic core using 22-gauge FNB needle was 70% and proportion (%) of optimal histologic core using 25-gauge FNB needle was 92% in second study[21] cuducted by Iwashita et al. A sample size of 56 pairs achieves 80% power to detect an odds ratio of 4.929 using a two-sided McNemar test with a significance level of 0.05. The odds ratio is equivalent to a difference between two paired proportions of 0.276. Assuming a 15% dropout rate, the final sample size was set at 66 pairs.

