All patients will undergo EUS-FNB with 22-gauge (Echotip ProCore; Cook Endoscopy Inc, Limerick, Ireland) and 25-gauge (Echotip ProCore; Cook Endoscopy Inc, Limerick, Ireland) needles subsequently for the same pancreatic lesion; the procedures will be performed by an experienced echoendoscopist ([name]) with a current volume of 750 EUS cases per year, including 150 or more FNA/FNB, using a well-established technique [17]. The FNB device will be made of a 140-cm stainless steel with a 5.2 F shaft ending with a beveled tip 4 mm in length within a spiral steel sheath surrounded by a Teflon cover. All procedures will be performed with a linear array echoendoscope (Olympus UCT 260, Olympus Co., Tokyo, Japan). After visualizing the target lesion in the endosonographic plane, the echoendoscopist will use color Doppler to identify the optimal position for puncture without intervening vessels between the needle and target lesion. The needle will be inserted into the target tissue under EUS guidance via the duodenum for pancreatic head and uncinate masses and via the stomach for pancreatic body and tail masses. Once the lesions will be well penetrated with the needle, the stylet will be removed; a 10-cm^3^ suction syringe will be applied to the needle hub, and 10 uniform back-and-forth movements will be performed within the lesion during each needle passage. The needle will be then withdrawn into the spiral steel sheath and detached from the echoendoscope. After two individual punctures, the first needle will be withdrawn into the catheter and removed; the procedure will be repeated in same fashion with the second needle. The FNB needle sequences will be randomly assigned in a 1:1 proportion based on a computer-generated random order (22- or 25-gauge first), and two punctures will be conducted for each needle respectively. The allocation sequence will be concealed using opaque sealed envelopes, and neither the cytopathologist nor the patients will be unaware of the treatment allocation.

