**12. Study goals**

**Primary study goal:**

The procurement rates of histologic cores that the cytopathologist ([name]) considered to be of optimal quality for histological evaluation of the needle gauge

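### Needle order is randomised but the planned McNemar test ignores it: the test stays valid, yet a chance imbalance between sequences would shift part of any order effect into the needle difference

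*Protocol*

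**What the plan says.** Section 4 of the protocol describes the trial as a "Single center, prospective, randomized, double-blinded corss-over study". Section 10 states that "The FNB needle sequences will be randomly assigned in a 1:1 proportion based on a computer-generated random order (22- or 25-gauge first" and describes the session: "After two individual punctures, the first needle will be withdrawn into the catheter and removed; the procedure will be repeated in same fashion". For the first needle, the first passage goes to cytology and the second to histology. If the second needle is handled the same way, its histology specimen comes from the fourth puncture of the lesion.

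The primary goal in section 12 is binary for each needle: "The procurement rates of histologic cores that the cytopathologist" judges to be of optimal quality. For this kind of endpoint section 13 says "McNemar tests were used to compare binary variables". Section 5 sizes the trial on a two-sided McNemar test (56 pairs, 66 after dropout). Neither section names a sequence or position term, and the intervention variables listed in section 15 do not include needle order.

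**The concern.** McNemar's test compares the two kinds of discordant pair without regard to which needle went first. The second needle enters tissue already punctured twice in the same session, so a different yield in second position is conceivable. The randomised factor that could separate a needle effect from a position effect is not used in the test that the protocol fixes.

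At stake is the reading of the primary result. If more analysed patients had the 25-gauge needle first than second, a general fall in yield for the second needle would look like an advantage of the 25-gauge needle; with the opposite imbalance it would hide one. Without results by order, a reader could not tell.

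**Working it through.** **Inputs from the protocol.** Optimal-core rates 92% (25-gauge) and 70% (22-gauge), two-sided 5% level, 56 analysable pairs, 66 with 15% dropout (sections 5 and 13); 1:1 random order (section 10).

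**Assumptions.** The protocol gives no order effect, so a fall of 0, 10 or 20 points for whichever needle is second is assumed. The two needles' outcomes are taken as independent within a patient.

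**1. The plan's own figure.** Discordant cells under independence: 0.92 × 0.30 = 0.276 and 0.70 × 0.08 = 0.056; ratio 0.276/0.056 = 4.929, the stated odds ratio. Exact McNemar power is 0.799 at 55 pairs and 0.808 at 56, so 56 is reproduced. 56/0.85 = 65.9, rounded up to 66.

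**2. Expected difference by sequence.** Let s be the fall in yield for the second needle.

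- 25-gauge first: 0.92 − (0.70 − s) = 0.22 + s
- 22-gauge first: (0.92 − s) − 0.70 = 0.22 − s

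The simple average of the two is 0.22 whatever s is. The pooled paired difference weights them by the numbers analysed, n₁ (25-gauge first) and n₂:

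pooled difference = 0.22 + s(n₁ − n₂)/(n₁ + n₂).

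| Split n₁/n₂ | s = 10 points | s = 20 points | Average over sequences |
|---|---|---|---|
| 28/28 | 22.0 | 22.0 | 22.0 |
| 33/23 | 22 + 10 × 10/56 = 23.8 | 22 + 20 × 10/56 = 25.6 | 22.0 |
| 23/33 | 20.2 | 18.4 | 22.0 |

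**3. How likely such a split is.** For X ~ Binomial(56, 0.5), P(|n₁ − n₂| ≥ 10) = 2·P(X ≥ 33) = 0.23. This holds for unblocked allocation.

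**4. Validity of McNemar.** Simulations with no needle difference (81% for both needles):

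- 33/33, order effects of 10, 20 and 30 points: mean difference 0.000; asymptotic type I error 4.9%, 3.8% and 2.6%.
- Simple 1:1 randomisation, averaged over splits: about 5.3%.
- Conditional on 40/26 (an imbalance this large or larger has 11% probability): bias of about 2, 4 and 6 points; asymptotic type I error 6%, 8% and 11%.

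**5. Power at 56 pairs, 92% vs 70%.** The adjusted analysis is the mean within-patient difference averaged over the two sequences, tested with a pooled-variance t on 54 df.

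| Order effect, split | Exact McNemar | Asymptotic McNemar | Adjusted |
|---|---|---|---|
| 0, 28/28 | 81% | 86.8% | 86.7% |
| 0, 33/23 | 81% | 87.0% | 85.6% |
| 20 points, 28/28 | 63% | 73% | 75% |
| 20 points, 23/33 | 46% | 57% | 74% |

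The like-for-like comparison is asymptotic against adjusted. When balanced, the gain is 0 to 3 points; the Mainland-Gart test gains about 1 point at a 20-point order effect. With no order effect, adjusting costs at most 87.0 − 85.6 = 1.4 points.

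**6. Differential carry-over.** Suppose only the 25-gauge needle loses 10 points when second. The sequence differences are 0.92 − 0.70 = 0.22 and 0.82 − 0.70 = 0.12. At 28/28 the pooled and the averaged estimate are both 0.17, and power is about 60% for both. A first-needle-only comparison, 28 vs 28 at 92% vs 70%, has about 42% power (Fisher) or 57% (uncorrected chi-square).

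**The case against.** The strongest reply is that the planned test is valid and matches the sample-size basis, and that tables by sequence are commonly left to a SAP, which is not shown here. Validity and the match both stand. The SAP argument stands for the extra tables but not for the choice of test: sections 5 and 13 fix an unstratified McNemar test in the protocol itself.

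A reader might also infer more than the documents support:

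- *That pooling leaves an order effect in the result.* It does so only when the realised sequences are unequal. Randomised order removes a common order effect in expectation, and the test keeps its level.
- *That pooling costs 12 points of power (63% against 75%).* Most of that gap is exact against asymptotic testing. The fall from about 87% to 75% comes from the assumed lower yields and affects the adjusted analysis too.
- *That stratifying removes differential carry-over.* Step 6 shows that it does not; this is a limit of the design.
- *That the protocol predicts a larger drop after the 22-gauge needle.* Section 3 says only that "blood and cellular debris contamination complicate cytopathological interpretation, a common occurrence with the widely used 22-gauge needle". That concerns reading the specimen, not whether a later needle obtains a core.
- *That dropout will unbalance the sequences.* The causes in section 17 concern reaching or seeing the lesion and have no evident link to which needle goes first, so they give no systematic imbalance.

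Finally, section 10 does not mention blocking, but silence does not mean that allocation is unblocked. If it is blocked, an imbalance of 10 becomes much less likely.

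**Conclusion.** The point holds as a conditional weakness in the analysis, not as an error that invalidates the primary test. The protocol randomises needle order and then fixes a test that disregards it. If the analysed sequences split 33/23, the pooled difference moves by 1.8 points for a 10-point order effect and 3.6 points for a 20-point one, against a true 22; the difference averaged over sequences does not move. The 23% chance of an imbalance at least that large assumes unblocked allocation, and the order effects are assumptions with no figure in the protocol. With balanced sequences little is lost. Differential carry-over would bias either analysis; results by order can only make it visible, with low power.

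**What to change.** In section 13:

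- Compare optimal-core rates with a paired analysis stratified by randomised sequence, for example the Mainland-Gart test.
- Report the needle difference as the average of the two sequence-specific differences, with a 95% CI.
- Tabulate discordant pairs by sequence, and optimal-core rates by needle and position (first or second).
- Keep the unadjusted McNemar test alongside, as the basis of the sample size in section 5.

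If the sponsor prefers McNemar as primary, the minimum is to pre-specify the stratified analysis as a sensitivity analysis, with the same table. A first-needle-only comparison may be shown descriptively, with its low power stated. Needle order should be added to the intervention variables in section 15, and section 10 should say whether allocation is blocked.

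The cost is a few sentences, one table and at most about 1.4 points of power if there is no order effect. Procedures and sample size do not change.

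### Section 13 assigns an independent-groups t-test to all continuous variables in a design that pairs both needles within each patient (minor; no stated endpoint is affected)

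*Protocol*

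**What the plan says.** Section 4 of the Protocol describes the study as "Single center, prospective, randomized, double-blinded corss-over study" and counts the sample in pairs. Section 10 has every patient sampled with 22-gauge and 25-gauge "needles subsequently for the same pancreatic lesion". Only the order is randomised: "The FNB needle sequences will be randomly assigned in a 1:1 proportion". The sampling effort is fixed for each needle: "two punctures will be conducted for each needle respectively", and "10 uniform back-and-forth movements will be performed within the lesion during each needle passage".

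Section 13 sets out the tests in one sentence. Its first half reads "McNemar tests were used to compare binary variables" and its second half "two-sample *t*-tests were used to compare continuous variables". It does not say which continuous variables are meant or which groups are compared.

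The primary goal in Section 12 is a rate: "The procurement rates of histologic cores that the cytopathologist" judges optimal. The secondary goals are diagnostic performance, technical failure and procedure-related adverse events.

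**The concern.** A two-sample t-test treats its two sets of values as coming from different, unrelated patients. In this study no patients receive only one of the needles; the two values for a needle comparison come from the same patient and the same lesion. The plan recognises this for binary variables, since McNemar's test makes sense only for paired data, and then drops the pairing for continuous variables in the same sentence.

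At stake is the error term of any continuous within-patient comparison. Two samples from one lesion, or two readings from one patient, will usually be positively correlated. The independent-groups standard error is then too large, the test rejects too seldom, and a real difference may be reported as absent. The efficiency that the cross-over design buys is lost for those variables.

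**Working it through.** **1. The plan's own figure, to see whether the t-test enters it.** Section 5 takes core rates of 70% (22-gauge) and 92% (25-gauge). If the two results within a patient are treated as independent, the discordant probabilities are 0.30 × 0.92 = 0.276 and 0.70 × 0.08 = 0.056, and their ratio is 0.276/0.056 = 4.929, the stated odds ratio. The exact two-sided McNemar test at 5% has 79.9% power with 55 pairs and 80.75% with 56, so the stated 56 pairs are reproduced. Allowing for 15% dropout, 56/0.85 = 65.9, rounded up to 66. The sample size rests on the paired binary test alone.

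**2. Which variables the t-test sentence could reach** (Sections 8, 12 and 15):

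- Primary and listed secondary goals: all binary or rates, so not reached.
- Weight, height and lesion size: one value per patient or lesion. These can be compared only between the two sequence groups, where the two-sample test is correct.
- Number of passes needed for diagnosis: a count that could be compared by needle, though with two punctures per needle it can take very few values.
- Number of to-and-fro movements: fixed at 10, so there is no planned variation to test.
- Quality of histologic specimens: no scale is stated. It is reached only if it is scored numerically.
- Temperature, blood pressure, blood count and chemistry: recorded before and after the procedure. They are reached only if the change is tested, and the Protocol plans no such test.

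**3. Size of the error where the sentence applies.** Assume equal variance s² for both measurements and n = 66 pairs.

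- Paired standard error: sqrt(2s²(1−rho)/n).
- Independent-groups standard error: sqrt(2s²/n).
- Ratio, independent to paired: 1/sqrt(1−rho).

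The two-sample test rejects beyond t(0.975; 130 df) = 1.978. Expressed on the scale of the paired statistic, which has 65 df, that cut-off becomes 1.978/sqrt(1−rho). The true size is the two-sided tail of t(65) beyond it. For power, fix the difference at which the paired test has 80% (noncentrality 2.844 with cut-off 1.997) and evaluate the noncentral t beyond the inflated cut-off.

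| rho (assumed) | SE ratio | Effective cut-off | True size | Power where paired has 80% |
|---|---|---|---|---|
| −0.2 | 0.91 | 1.806 | 7.6% | 85% |
| 0 | 1.00 | 1.978 | 5.2% | 81% |
| 0.3 | 1.20 | 2.365 | 2.1% | 68% |
| 0.5 | 1.41 | 2.798 | 0.7% | 52% |
| 0.7 | 1.83 | 3.612 | 0.06% | 24% |

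Simulation with 20,000 trials per setting at 66 pairs gives sizes of 2.2%, 0.6% and 0.03% for rho 0.3, 0.5 and 0.7, in line with the table. With 56 pairs the results are almost the same (rho 0.5: size 0.7%, power 52%).

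**The case against.** The strongest defence is that nothing the trial sets out to show depends on this sentence. Every stated goal is binary or a rate, and binary comparisons get McNemar's test. Most listed continuous variables belong to the patient, not to a needle. Because both needles are used in one session, post-procedure values cannot be attributed to either. Sequence is randomised 1:1, so comparing patient-level variables between the two sequence groups is a natural use of the two-sample t-test, and there it is right. Which variable goes to which test is often settled in a statistical analysis plan, which is not at hand.

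Most of this stands, and it limits the point. A reader might infer that the P-values for the needle comparison in general are wrong. The document does not support that, because the needle comparisons named as goals are McNemar-based. A reader might also infer that the plan mis-analyses amylase before and after the procedure. That is not supported either: amylase enters the endpoints only as a threshold within the definition of pancreatitis, and no before/after test is stated. Nor is there a false-positive risk under positive correlation; the error then runs towards missed differences.

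What does not stand is the claim that nothing at all is affected. The Protocol has not left the choice open. It names the test for continuous variables without restriction, alongside a test that applies only to paired data. Number of passes by needle, a numeric quality score, or before/after values would all fall under that rule if they were compared.

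**Conclusion.** The sentence is wrong as written, and the point is minor. For any continuous or count variable compared within patients, the prescribed test uses a standard error that is off by 1/sqrt(1−rho). For rho from 0.3 to 0.7 that means a standard error 1.20 to 1.83 times too large, and power of 68% down to 24% where a paired test would have 80%.

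These figures rest on three assumptions: the rho range, which the Protocol does not give; equal variances and approximate normality; and 66 complete pairs. At rho = 0 the error essentially vanishes (size 5.2%), and at a negative rho it reverses. For a count with very few values, such as passes per needle, the t-based figures are only indicative.

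The primary analysis, the listed secondary endpoints and the figures of 56 and 66 pairs are not affected. The conclusion concerns supporting comparisons only, and only if they are made.

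**What to change.** Replace the second half of the test sentence in Section 13 with wording to this effect: continuous variables measured with both needles, or before and after the procedure if these are compared, will be analysed by paired t-test, or by Wilcoxon signed-rank test for small counts or clearly non-normal data; two-sample t-tests will be used only for patient-level variables compared between the two needle-sequence groups.

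If specimen quality is to be compared numerically by needle, state its scale in Section 15 so that it is clear which test applies.

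The cost is one or two sentences. No additional data or patients are needed, and the sample size does not change.

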**Secondary study goal:**

Diagnostic performance

Technical failure

Procedure-related adverse events

e.g. Technical failure was defined as any difficulties, including the inability of the needle to exit from the scope channel, mechanical rupture of the needle, and any needle malfunction that required a new needle.

Adverse events were defined as immediate or late bleeding, immediate or late perforation, over-sedation requiring reversal medication, or any other cardiopulmonary distress during or after EUS-guided sampling as observed by the endosonographer or recovery suite nurse or as reported by patients. Acute pancreatitis was defined as serum amylase levels ≥ 3-fold the upper limit of the normal range (>345 g/dL), and for newly developed or worsened pancreatic-type abdominal pain and tenderness with nausea/vomiting, >24 hours after the procedure.

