**17. Predictable cause of drop out**

The target lesion could not be reached because of anatomical alteration

Significant duodenal stricture

Collateral intervening vessels

Non-visualization of target lesion under echo-endoscopy

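### Diagnostic performance of each needle rests on a per-protocol analysis alone, so a needle that fails and gives no sample can drop out and make that gauge look more accurate than it is

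*Protocol*

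**What the plan says.** Protocol section 13 (Statistical analysis) states that the five diagnostic measures "of each needle were calculated based on per protocol analysis". It does not define the per-protocol set and gives no analysis of all attempts beside it.

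Three other places bear on who would be in that set:

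- Section 10 (Study procedure): every patient is sampled with both gauges in random order, and "two punctures will be conducted for each needle respectively". The first pass goes to cytology and the second to histology.
- Section 12 (Study goals): technical failure is a separate secondary goal. It covers "the inability of the needle to exit from the scope channel, mechanical rupture of the needle, and any needle malfunction that required a new needle".
- Section 17 (Predictable cause of drop out): the foreseen causes concern the patient or the lesion, for example "The target lesion could not be reached because of anatomical alteration". Needle failure is not among them.

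Nowhere does the protocol say whether a needle that yields nothing counts as non-diagnostic or is omitted.

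**The concern.** Failing to deliver a sample is part of how a biopsy needle performs. If a needle cannot be advanced in a patient who has cancer, it has not diagnosed that cancer. An analysis restricted to samplings completed as planned takes that attempt out of the failing needle's denominator, so its sensitivity and accuracy are estimated only where it worked.

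This would matter little if both gauges failed equally often. The protocol gives its own reason to think they might not. Section 3 refers to "mechanical friction of the needle-firing mechanism in larger-caliber needles in the torqued trans-duodenal position" and offers this as the reason for developing a more flexible 25-gauge device. The same section puts 60% to 70% of ductal adenocarcinomas in the head or uncinate process, and section 10 sends those lesions by the duodenal route. The attempts most exposed to the problem would thus be common and often malignant. At stake is a fair comparison of the needles on the secondary goal of diagnostic performance.

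**Working it through.** The protocol states no failure rate and no expected diagnostic performance for these needles, so there is no figure of its own to reproduce on this point. The size below is an illustration under stated assumptions.

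**Inputs**

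- s, sensitivity among attempts that gave a sample: 85% as the working value (assumption), with 75% to 92% as the range. That range is the one section 9 quotes for EUS-FNA, not for these biopsy needles.
- f, share of attempts in malignant lesions where the needle fails, is not rescued and gives no sample: 2%, 5% and 10% (assumptions).

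**Formula.** Per-protocol sensitivity is s. With every attempt in the denominator and a failure counted as not diagnosed, sensitivity is s × (1 − f).

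**Results for s = 85%**

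- f = 2%: 0.85 × 0.98 = 0.833
- f = 5%: 0.85 × 0.95 = 0.8075
- f = 10%: 0.85 × 0.90 = 0.765

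**Effect on the comparison.** Suppose both needles have sensitivity s when they work, one never fails and the other fails at rate f. Per protocol the difference is zero. Over all attempts it is s × f:

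| f | s = 75% | s = 85% | s = 92% |
|---|---|---|---|
| 2% | 1.5 points | 1.7 points | 1.8 points |
| 5% | 3.75 points | 4.25 points | 4.6 points |
| 10% | 7.5 points | 8.5 points | 9.2 points |

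**Dropping the pair instead of the needle.** If the whole patient is removed when one needle fails, the denominators stay equal and the pairing is intact. The failure still leaves the failing needle's record, so that needle's sensitivity is again s rather than s × (1 − f).

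**Measure by measure.** Sensitivity is raised as shown, and accuracy is raised in the same way when f is taken over all lesions. PPV does not move, because a needle without a sample makes no positive call. For specificity and NPV the effect depends on how a missing result is classified. That affects the remedy. If a failure were counted simply as not positive, a failed needle in a benign lesion would become a true negative. With an assumed specificity of 90% and 10% failures, specificity would rise to 0.90 × 0.90 + 0.10 = 0.91, which rewards the failure. Counted as not correct, it is 0.90 × 0.90 = 0.81.

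**The case against.** The strongest reply is that the exclusion is inferred. The per-protocol set is undefined, its definition could sit in a statistical analysis plan that is not at hand, and the listed drop-out causes would remove a patient for both needles alike. It stands that the protocol does not expressly remove technical failures. But the restriction to per protocol is itself stated. With two punctures required per needle, a needle that gave none is outside the set on the usual meaning of the term.

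Three further points stand and limit the size:

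- Technical failure is not the same as no sample. The definition includes "any needle malfunction that required a new needle", and the replacement may complete both passes. Only unrescued failures count in the arithmetic above.
- The friction remark in section 3 cites references 10 to 13, whose titles all concern Trucut biopsy, one of them a 19-gauge needle. It is a motive for expecting a difference, not evidence that the 22-gauge needle used here fails more often.
- Technical failure is reported as its own goal, so a reader would see it. That does not correct the accuracy figures.

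A reader might also infer that the primary endpoint loses power because failures would be deleted from the core-procurement comparison. The documents do not support this. Section 13 ties per protocol only to the diagnostic measures, and no such rule is stated for the primary goal. Nor do the documents say whether the 70% core rate used in section 5 for the 22-gauge needle already includes failures. Likewise, a reader might infer that the two needles must end up with different denominators. That follows only if the single needle, not the pair, is dropped.

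**Conclusion.** The concern holds for the secondary diagnostic-performance goal. Using a per-protocol analysis as the only basis allows a needle's own failures to be left out of its sensitivity and accuracy, and the comparison is biased towards the needle that fails more if failure differs by gauge. Under the assumed 2%, 5% and 10% unrescued failures, an 85% sensitivity overstates the all-attempts value by 1.7, 4.25 and 8.5 points. If such failures are rare the effect is small. The conclusion rests on the ordinary meaning of per protocol and on assumed failure rates. It does not extend to PPV or to the primary endpoint. The change is worth making because it is cheap and gives a better estimate, not because the trial's main result is at risk.

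**What to change.** Replace the per-protocol basis in section 13 with wording to this effect:

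- The main analysis of diagnostic performance includes all patients in whom puncture was attempted, with both needles kept in the paired comparison. Results are reported by gauge; only the order of the needles is randomised.
- A needle that yields no sample, or a non-diagnostic one, counts as not correctly diagnosed for that needle in sensitivity, specificity and accuracy, whether the lesion is malignant or benign. It is never counted as a true negative.
- A failure rescued by a new needle of the same gauge is classified by the sample obtained, and is still reported as a technical failure.
- Patients in whom neither needle could be attempted, for the causes in section 17, are excluded for both needles.
- The per-protocol analysis, with its set defined, is kept as a sensitivity analysis.

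The cost is a few sentences and no extra data. Reported accuracy will be slightly lower.
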